### Investigations

An overview including the time-frame of investigations is shown in the Fig. 1.

**Fig. 1 Fig1:**
[figure not shown]
SPIRIT figure of the Stockholm Myocardial Infarction with Normal Coronaries study 2. CMR=Cardiac magnetic resonance imaging; CTA = Computed Tomography Angiography; Echo = Echocardiography; QoL = Quality-of-Life

CMR is performed by a Siemens Aera 1,5 T® including the following steps: 1. Scout through thorax with transversal, coronar and sagital stacks with trueFISP-sequences, without ECG triggering. 2. Vertical long-axis through left ventricle with trueFISP without ECG triggering. 3. Horisontal long-axis through left ventricle with trueFISP cine, with ECG triggering. 4. Pre-contrast T1-mapping with MOLLI (Modified Look-Locker Inversion recovery) sequence containing several ECG-triggered single shot trueFISP in end-diastole with different times of inversion. Sequences should be sampled in short-axis, 2,3 and 4 chamber view stacks. 5. Pulmonary transition time, saturation recovery trueFISP perfusion, single slice short-axis through left atrium, 20 mm slice thickness, without ECG triggering, parallel -imagination with GRAPPA factor 4 with 2 ml bolus of contrast (Dotarem®) + 20 ml NaCl, 4 ml/s injected by automated injector. 6. Further contrast injection (Dotarem®) to double dose injected by automated injector. 7. Cine trueFISP in short-axis, 2,3 and 4 chamber view stacks to study left ventricular function. 8. TI-scout followed by phase sensitive inversion recovery (PSIR) late gadolinium enhancement (LGE) in short-axis, 2,3 and 4 chamber view stacks, to study infarction and microvascular obstruction. Should be made at least 10 min after contrast injection. 9. MOLLI post-contrast T1-mapping in short-axis, 2,3 and 4 chamber view stacks*.* 10. Phase contrast-based flow measurement sequence, without breath-holding, through aorta ascendens and pulmonary artery.

*Acute myocardial infarction* is defined as localized subendocardial late gadolinium enhancement (LGE) with corresponding oedema (T1 mapping).

*Acute myocarditis* is defined as diffuse mainly subepicardial LGE with corresponding oedema (T1 mapping).

*Acute TCM* is defined as presence of myocardial oedema (T1 mapping) and/or transient wall motion abnormalities with circumferential distribution with absence of corresponding LGE and coronary artery distribution.

Computed tomography angiography (CTA) is performed using a 64-slice computed tomography scanner with ECG-triggered, prospective technique and with parameter settings resulting in submillimeter isotropic voxels. Patients with a heart rate > 65 beats/min will be given betablockers, orally or intravenously, before the scan. Patients with a systolic blood pressure > 100 mmHg will be given sublingual nitroglycerine before the scan. First, a non-enhanced scan will be performed enabling measurement of calciumscore. Second, nonionic iodinated contrast agent will be administered as a standard bolus volume but with individually measured time of delay. Data within the end-diastolic phase will be reconstructed in 5% steps and thereafter analyzed using dedicated software with post-processing tools such as multiplanar reformation, curved multiplanar reformation and maximum intensity projection. Images will be analyzed semi-quantitatively regarding number, location, severity and quality of coronary plaques by 2 observers who are blinded to the clinical information where disagreement will be solved by consensus.

Echocardiography is performed on GE Vivid E9® scanners. All registrations besides CW/PW Doppler consist of three cardiac cycles. The ejection fraction will be calculated using Simpson’s rule. Regional wall motion will be classified by visual inspection of wall thickening, classifying segments with less than 30% thickening as hypokinetic, less than 10% as akinetic, and segments with systolic thinning or eccentric excursion as dyskinetic. 2D loops of from the three apical views are analyzed using the longitudinal 2D strain Q-analysis module in EchoPAC BT11.2® (GE, Horten, Norway). After marking the myocardial borders as the region of interest (ROI), the application semi-automatically generates strain curves and peak systolic strains, and also automatically calculates the proportion of shortening that takes place after aortic valve closure (post systolic index). Furthermore the temporal derivation to strain rate can be performed. The software calculates global averages as well as segmental values for all variables, and both will be recorded. Color coded tissue Doppler loops from the same apical views will be analyzed in the TDI Q-analysis module. ROIs will be placed in the two basal segments in each view, in order to measure the peak systolic and early diastolic velocities, as well as the timing of the events of the cardiac cycle, which will be used to calculate the myocardial performance index for the left ventricle, and in the same manner for the right ventricle. The standard diastolic parameters of mitral inflow velocities, E/E’, and pulmonary venous flow will be measured. The E waves acquired during free breathing and after the Valsalva maneuver will be analyzed in a custom LabVIEW® (National Instruments, Austin, USA) interface where, by fitting the curve generated by the equation for a simple harmonic oscillator to the maximum velocity envelope of each E wave, the equation constants *k*, *c*, and *x* are calculated. These constants correlate closely to chamber stiffness, viscoelastic energy loss and load, respectively. Furthermore, the results are used to calculate the time constant of isovolumic chamber relaxation (*tau*), the stiffness and relaxation components of the deceleration time of the E wave, a load independent index of diastolic filling and stiffness.

Laboratory investigations are performed by routine clinical chemistry. Haematology, electrolytes, cystatin C, glucose, lipids and NT-proBNP, thyreoid function tests, hsTroponinT, D-dimer, metoxycatecholamines and urine albumin/creatinine ratio, oral glucose tolerance test (75 g with measurement of glucose after 2 h), HbA1C and cortisol in saliva (morning and evening). All patients will be investigated haematologically to exclude proneness to thromboembolism and systemic lupus erytematosus at 6 months according to the routine of Karolinska University Laboratory.

Quality-of-Life is investigated: Rand 36 (former SF-36), Multidimensional Fatigue Inventory (MFI-20), Perceived Stress Scale (PSS-14) and Hospital and Anxiety Depression Scale (HADS).

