The Stockholm Myocardial Infarction with Normal Coronaries (SMINC) study was a study with the primary aim to investigate the role of endothelial function in MINOCA [4]. The results showed that endothelial function and common carotid intima-media thickness were normal when compared to controls. Furthermore, the risk factor profile resembled Coronary Heart Disease (CHD) controls with the exception for a non-atherogenic lipid profile. In the SMINC study, patients with myocarditis were excluded by CMR imaging. Other exclusion criteria were previous myocardial infarction, known cardiomyopathy, severely impaired renal function and Chronic Obstructive Pulmonary Disease (COPD) as well pulmonary embolism and type 2 myocardial infarction. The screening phase of the SMINC study of all patients investigated with CMR imaging showed that it was possible to assign a definitive diagnosis to 50% of the patients by performing CMR imaging and adding clinical information in particularly on the occurrence of Takotsubo stress CardioMyopathy (TCM) [5]. Major limitations of the CMR imaging in the SMINC study were that it was performed in median 12 days after the acute event and that the latest CMR imaging technique including T1 mapping to detect oedema was not performed. Furthermore, at that time there was no clear CMR imaging-based diagnosis for TCM. The second SMINC study (SMINC-2) is on-going with the *primary aim* to give 70% of the patients a definite diagnosis purely on the basis of the CMR imaging results. To be able to do this, the protocol states that CMR imaging should be performed 2-4 days after hospitalisation because of MINOCA and to include T1 mapping in addition to T2 oedema sequences. An overall *secondary aim* is to test a protocol on how to investigate MINOCA patients including further characterisation of these patients with emphasis on coronary imaging and stress. The objectives of this paper are to describe the rationale behind the SMINC-2 study and to discuss the protocol of investigation of MINOCA patients in the light of the recently published position paper [3].

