## Methods/design

The study design is an open non-randomised multi-center study using historical controls from the SMINC study for comparison. The primary aim is to prove that patients investigated with CMR imaging can achieve a definite diagnosis in 70% of all MINOCA cases entirely by imaging (Clinical Trials NCT02318498). By including 150 patients, we will have >80% chance to prove that the diagnostic accuracy can be improved by 20 absolute % with a *p*-value of less than 0.05 when compared with our previous sample [5]. By January 1st 2017, 75 patients have been included. The study is supported by grants provided by the Stockholm County Council (ALF project) and Swedish Research Council.

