## Discussion

The primary objective of the present paper is to describe the rationale behind the SMINC-2 study that has the aim to test if early CMR imaging using the latest technique can give more than 70% of all MINOCA patients a CMR imaging-based diagnosis. The main diagnoses that are possible to acquire are myocarditis, TCM and “true” myocardial infarction. Our previous meta-analysis of CMR imaging findings in MINOCA showed that one third of the patients had myocarditis and 20% had “true” myocardial infarction [2, 8]. These new studies shows that early CMR imaging (median 3, respectively 6 days) with conventional T2 oedema sequences gave the patients a definite diagnosis in 90%, respectively 87% of the cases. The reasons for these extraordinary figures are possibly due to study design where the results by Emrich and coworkers [7] are limited due to the retrospective design possibly including patients with already known or suspected diagnosis whereas in the prospective study by Pathik and co-workers [8] all-comers were included without exclusion criteria. Both studies were able to diagnose TCM by CMR imaging (10%, respectively 27%) thereby improving the diagnostic performance of CMR imaging. The results of the meta-analysis and the recent studies [2, 7, 8] support the idea that early CMR imaging with the latest CMR imaging technique can give the diagnosis in the vast majority of MINOCA patients thus being an important diagnostic tool as pointed out in the recent position paper by the ESC [3].

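### The Takotsubo criterion lets LGE-negative, non-coronary oedema count as a definite diagnosis with normal wall motion, and leaves open whether that oedema must be circumferential

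*Protocol article*

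**What the plan says.** The primary aim (Protocol article, Methods/design) is that patients examined with CMR "can achieve a definite diagnosis in 70% of all MINOCA cases entirely by imaging". The Discussion names three main diagnoses that CMR can give: myocarditis, TCM and true infarction. The definitions stand under Investigations, after the list of CMR steps:

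- For TCM the article asks for "presence of myocardial oedema (T1 mapping) and/or transient wall motion abnormalities with circumferential distribution with absence of corresponding LGE". The same sentence goes on to rule out findings that follow a coronary artery distribution.
- The entry for myocarditis reads differently: it "is defined as diffuse mainly subepicardial LGE with corresponding oedema (T1 mapping".
- The entry for infarction likewise needs enhancement: it "is defined as localized subendocardial late gadolinium enhancement (LGE) with corresponding oedema (T1 mapping".

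On the comparator, the Background says that in SMINC-1 "it was possible to assign a definitive diagnosis to 50% of the patients by performing CMR imaging and adding clinical information", the clinical information being in particular about TCM. It adds that T1 mapping was not done in SMINC-1 and that "at that time there was no clear CMR imaging-based diagnosis for TCM".

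**The concern.** Two of the three diagnoses need a positive LGE finding. The third needs LGE to be absent, and the *and/or* removes any need for a wall motion abnormality. A patient scanned at day 2 to 4 with raised T1, no LGE and normal cine images can therefore be recorded as definite TCM if the distribution terms are met. If the oedema is in fact inflammatory, the myocarditis definition is closed to that patient, and TCM is the only defined category left.

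The primary endpoint counts patients with a definite diagnosis, so a wrong label scores the same as a right one. The route depends on T1 mapping, which SMINC-1 did not have. Part of any gain over SMINC-1 could then come from a wider label and not from better diagnosis, and a single pooled yield would not show how much.

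**Working it through.** **1. The definitions side by side** (Investigations)

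| Diagnosis | Oedema | LGE | Wall motion abnormality |
|---|---|---|---|
| Infarction | required | required, subendocardial | not mentioned |
| Myocarditis | required | required, mainly subepicardial | not mentioned |
| TCM | one of two alternatives | corresponding LGE must be absent | the other alternative |

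On any reading of *and/or*, TCM can be assigned without a wall motion abnormality. Oedema without LGE can meet neither of the other two definitions.

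**2. What the distribution terms restrict**

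- Strict reading: the circumferential and non-coronary terms govern oedema and wall motion alike. Focal or patchy oedema does not qualify. Circumferential, non-coronary oedema with normal wall motion does.
- Loose reading: the circumferential term belongs only to wall motion, the nearer noun. Non-coronary oedema without LGE then qualifies even if it is not circumferential.

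The oedema-only route is open on both readings; they differ in its width. The grammar does not decide between them.

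**3. The plan's own figure**

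Methods/design states more than 80% power with 150 patients for a 20-point gain at p < 0.05. The gain runs from 50% (Background) to 70% (Methods/design). The number of controls and the sidedness of the test are not given. With n1 controls at p1, n2 = 150 new patients at p2 and pooled proportion p,

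power = Φ{[(p2 − p1) − 1.96·√(p(1−p)(1/n1 + 1/n2))] / √(p1(1−p1)/n1 + p2(1−p2)/n2)}.

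For an assumed 75 controls, p = (37.5 + 105)/225 = 0.633. The two standard errors are 0.0682 and 0.0688, so power = Φ[(0.20 − 1.96 × 0.0682)/0.0688] = Φ(0.97) = 83%. With an assumed 150 controls it is 95%. The stated figure is consistent with 66 or more controls two-sided, or 47 or more one-sided. It is not in dispute here.

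**4. How much oedema-only labels could matter**

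The article gives no share of patients who would be labelled on oedema alone, so the shares below are assumptions. Five per cent is 0.05 × 150 = 7.5 patients, and 5/20 is a quarter of the planned gain. Taking such labels out of a 70% yield, with the denominator kept at 150, gives:

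| Oedema-only share | Patients of 150 | Yield without them | Power vs 50%, 75 controls | Power vs 50%, 150 controls |
|---|---|---|---|---|
| 0% | 0 | 70% | 83% | 95% |
| 5% | 7.5 | 65% | 58% | 75% |
| 10% | 15 | 60% | 30% | 41% |
| 15% | 22.5 | 55% | 11% | 14% |

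For the whole 20 points to be an artefact of labelling, with a genuine yield of 50%, the share f of the remaining patients labelled on oedema alone must satisfy 0.50 + 0.50·f = 0.70. So f = 0.40, or 30 of 75 patients. That is a large share, and nothing in the article suggests it.

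**The case against.** The strongest reply is that the definition is narrower than a quick reading suggests. A reader might infer that any oedema without LGE is enough for TCM. The full sentence does not support that: it excludes a coronary artery distribution and, on the strict reading, requires the oedema to be circumferential. Non-specific patchy oedema would then fail. This stands, and it limits the point to oedema that meets the distribution terms. It does not close the route.

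Second, a reader might infer that TCM was missing from the SMINC-1 rate. It was not: the 50% included TCM identified with clinical information, a source that the imaging-only endpoint of SMINC-2 gives up. The two rates therefore rest on different TCM rules, and the net direction of all these differences together is not known. What stands is narrower: the oedema-only branch by itself works only upwards and exists only in the new study.

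Third, the Discussion says of two early-CMR studies that "Both studies were able to diagnose TCM by CMR imaging (10%, respectively 27"%. It is tempting to treat this 17-point spread as the size of the problem. The article does not support that. These are total TCM rates from one retrospective study and one prospective all-comer study, both with conventional T2 sequences, and their TCM criteria are not given.

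Fourth, a reader might expect mislabelled patients to blur a TCM subgroup analysis of stress or quality of life. No such analysis is described; those measures are announced for MINOCA patients as a whole.

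Finally, early scanning with T1 mapping is the study's declared means of improving on SMINC-1, and wall motion may have recovered by the scan. Making a wall motion abnormality compulsory could discard true TCM. That is a fair argument against tightening the definition outright. It is not an argument against showing the class separately. T1 thresholds and reading rules may well be in the full protocol, but the *and/or* rule is stated in the article itself.

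**Conclusion.** The point holds in limited form. As written, LGE-negative, non-coronary oedema can score as a definite diagnosis with normal wall motion, and whether it must be circumferential is left open. LGE-negative inflammatory oedema that meets the distribution terms has no other category. Relative to a count without this branch, the SMINC-2 yield can only be higher.

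That the yield is in fact inflated is an inference that the article cannot confirm. It depends on how many patients are labelled on oedema alone and how many of those do not have TCM, and neither is given. The 7.5 patients per 5% follows from the planned 150; the power figures also assume 75 or 150 controls and a two-sided test. Within those assumptions a share of 5 to 10% would be enough to change how the comparison is read. The planned power and the overall design are not called into question by this point.

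**What to change.** Make three changes to the endpoint definition and its reporting:

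1. State that the circumferential and non-coronary terms apply to the oedema as well as to wall motion.
2. Record TCM based on oedema alone, with normal wall motion on the step 7 cine images, as a separate class.
3. Report the primary yield and its comparison with SMINC-1 both with and without that class. In the second version, keep these patients in the denominator as undetermined.

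The cost is a few sentences and one extra field in the reading form, because T1 maps, LGE and cine images are already part of the CMR protocol. By 1 January 2017, 75 patients had been included, so the class should also be assigned to them, before the comparison with SMINC-1 is made. The downside is that the yield without the class may leave out true TCM whose wall motion had recovered by the scan. That figure is therefore conservative, and the two should be read together.

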## Discussion

The primary objective of the present paper is to describe the rationale behind the SMINC-2 study that has the aim to test if early CMR imaging using the latest technique can give more than 70% of all MINOCA patients a CMR imaging-based diagnosis. The main diagnoses that are possible to acquire are myocarditis, TCM and “true” myocardial infarction. Our previous meta-analysis of CMR imaging findings in MINOCA showed that one third of the patients had myocarditis and 20% had “true” myocardial infarction [2, 8]. These new studies shows that early CMR imaging (median 3, respectively 6 days) with conventional T2 oedema sequences gave the patients a definite diagnosis in 90%, respectively 87% of the cases. The reasons for these extraordinary figures are possibly due to study design where the results by Emrich and coworkers [7] are limited due to the retrospective design possibly including patients with already known or suspected diagnosis whereas in the prospective study by Pathik and co-workers [8] all-comers were included without exclusion criteria. Both studies were able to diagnose TCM by CMR imaging (10%, respectively 27%) thereby improving the diagnostic performance of CMR imaging. The results of the meta-analysis and the recent studies [2, 7, 8] support the idea that early CMR imaging with the latest CMR imaging technique can give the diagnosis in the vast majority of MINOCA patients thus being an important diagnostic tool as pointed out in the recent position paper by the ESC [3].

A secondary objective of the present paper is to discuss the protocol of investigation of MINOCA patients in the light of the recently published position paper by the ESC [3]. In the position paper, a left ventriculogram or echocardiography is recommended if MINOCA is found during coronary angiography. This is recommended routinely by our local guidelines and will therefore be performed in the present study. Further invasive studies, suggested in the position paper, to exclude ruptured plaques, coronary dissections, microvascular dysfunction and coronary spasm are not routinely performed. The value of these investigations has to be proven before they can be recommended. Instead, in the present study a non-invasive CTA is performed 1 month after the acute event. The timing was made to decrease the risk for contrast-induced nephropathy after investigations with coronary angiography, including left ventriculography, and CMR. This investigation has the advantage that it can detect plaques not visible on invasive coronary angiography. It can also to some degree determine if the plaque is stable or unstable [9]. CTA will make it possible to investigate the cause of “true” myocardial infarction by studying myocardial infarction determined by CMR imaging in relation to supplying coronary artery. Furthermore, CTA is an accurate method to exclude coronary dissections [10]. Unfortunately, there are no reliable non-invasive examinations to exclude microvascular dysfunction and coronary spasm. Other investigations that are performed in SMINC-2 suggested by the position paper [3] include sampling of catecholamines to exclude pheocromocytoma, D-dimer to exclude pulmonary embolism and tests to exclude inherited causes of thromboembolism. The value of the results of all these investigations will be determined at the end of the study and the results will most likely support or refute the algorithm suggested by the recent position paper.

### Strength and limitations

The major strengths of SMINC-2 are the fairly high number of patients included from several hospitals being representative for a north European population and in comparison with several previous studies it is prospective and the first one with a control group. Limitations include the fairly strict age criteria and that it will not include patients with near significant coronary artery stenosis to be able to have the SMINC study as a control group. The reasons for the strict age criteria in the SMINC study were that it was unlikely that all patients would receive a coronary angiography if patients were below 35 and above 69 years of age. The reason for the lower age limit is that the likelihood is much higher for myocarditis than CHD and thus the diagnosis would be made without a coronary angiography. Regarding the upper age limit, many patients 70 years and older with suspected CHD were treated conservatively at the time of the start of the SMINC study 10 years ago. This together with the fairly strict inclusion and exclusion criteria may somewhat limit the representativity of the study.

